#### **3.3 Recruitment and inclusion**

The practical aspects of the study and main research are carried out at the Respiratory Research Units, Department of Respiratory Medicine at Hvidovre, Bispebjerg and Herlev/Gentofte University Hospital and by their investigators, primarily postdoctoral fellow, PhD [name], Associate professor, MD [name], Associate professor, Associate professor, MD [name], Associate professor, Senior researcher, [name], Professor, DSc., MD [name] and with support from the departments' VIP, TAP and clinical staff.

*Please read “section 5 - recruitment of subjects and informed consent” for recruitment details.*

#### **3.4 Criteria for participation**

##### **3.4.1 Inclusion criteria**

- Indication for pulmonary rehabilitation according to national guidelines
- Unable to access and participate in the conventional out-patient hospital- or community-based PR when offered during routine consultation
- A post-bronchodilator ratio FEV1/FVC <70% (confirmed physician diagnosis of COPD)
- A post-bronchodilator FEV1 <80% (degree of airway obstruction) corresponding to GOLD grade 2-4 (moderate to very severe)
- GOLD group B, C, D corresponding to severe respiratory symptoms and/or frequent acute exacerbations

- Able to stand up from a chair (height 44-46cm) and walk 10 meters independently (with or without a walking aid)
- Able to lift both arms to a horizontal level with a minimum of 1 kilogram's dumbbells in each hand

### **3.4.2 Exclusion criteria**

- Participation in conventional PR in the past 24 months
- Cognitive impairment - unable to follow instructions
- Impaired hearing or vision – unable to see or hear instruction from a tablet
- Unable to understand and speak Danish
- Comorbidities where the exercise content is contraindicated  
(ie. treatment for diabetic foot ulcer, active cancer treatment, life expectancy <12-months)

### **3.5 Data collection, assessment, and follow-up (table 1)**

The primary daily project management is carried out by the research project-manager ([name]). In addition, a project group (co-investigators), consisting of medical doctors and project nurses from the departments involved, will assist the project manager with the recruitment, sampling, and follow-up of patients. All medical decisions regarding patients will be taken by a medical doctor responsible for the treatment. Data is collected in RedCAP electronic Case Report Forms (eCRF), specific to each patient. Patients are continuously assessed against the study inclusion and exclusion criteria by the clinical staff (nurses, physicians).

The study data includes data from: socio-demographics, ethnicity, body composition, physical (function, activity, muscle strength, balance) outcomes as well as self-reported symptoms of anxiety, depression, fatigue, pain, respiratory symptoms, quality of life, sleep-quality and individual qualitative interviews concerning patient experience with intervention and maintenance program. Data from National Health Data Authorities on rehabilitation, rehospitalization, length of stay and mortality are included in the trajectory analysis.

#### **3.5.1 Measures obtained from the journal**

- Existing available data from lung function test.
- Home-oxygen therapy
- Prescribed medication
- Gender
- Age
- Marital status
- Smoking status
- Body mass index (otherwise measured)
- COPD classification GOLD 1-4 and A-D
- If heart failure classified by NYHA I-IV

#### **3.5.2 Measures obtained from the National Health Data Authorities at 75-weeks follow-up**

- Length of hospital stay.
- Number readmissions
- Mortality
- Any other received rehabilitation from inclusion (visit 0) to final assessment (visit 3) 75-weeks follow-up.

- Charlson comorbidity index

### **3.5.3 Self-reported outcomes (baseline and at all follow-up visits)**

- COPD Assessment Test (CAT) - (respiratory symptoms)
- Hospital Anxiety and Depression Scale (HADS) – (Emotional symptoms)
- EuroQol-5D-3L (EQ-5D-3L) – (Quality of life – generic)
- Brief Pain Inventory (BPI) – (Body pain- intensity/location)
- Multidimensional Fatigue Inventory (MFI-20) – (Perceived fatigue)
- Pittsburgh Sleep Quality Index (PSQI) – (Sleep Quality)

Approximately ≈30 patients will additionally be invited to participate in individual qualitative interviews concerning their personal experiences with intervention and maintenance programs. Data is collected continuously during the intervention period (phase-1) and the maintenance period (phase-2).

### **3.5.4 Physical function outcomes (baseline and at all follow-up visits)**

- ActivePAL triaxial accelerometer (PAL) – (Physical activity)
- 6-minute walk test (6MWT) – (walking capacity)
- 30-second sit to stand (30-sec-STS) – (leg muscle strength)
- Short Physical Performance Battery and (SPPB) – (function and frailty)
- Hand-grip strength (Jamar dynamometer) – (muscle strength upper extremity)

***Please read appendix 1. for information on the test procedure from the physical functioning test (Danish)***

## **3.6 Sample size and statistics**

*(performed by biostatistician [name], Clinical Research Centre, University Hospital Hvidovre)*

Three primary pairwise comparisons are made in the study, equivalence test between the two interventions and the superiority test for each intervention compared to the control group for the primary outcome of respiratory symptoms (COPD assessment test). Sample size estimation for the equivalence is based on a t-test with equivalence margin of -2.5 to 2.5 (clinically relevant difference), standard deviation (SD) of 4.5, power of 80% and significance level of 5%, and estimated 56 patients necessary in each group. For both, superiority tests a minimal clinical difference of 2.5, SD of 4.5, power of 80% and significance level of 5% were used in a two-sample t-test, with fixed sample of 56 patients in the intervention groups. This yields a necessary size of 36 patients in the control group. The sample size is increased by 25% in each group to account for expected withdrawal and loss of power from adjustment and thus a total of 185 (70/70/45) patients. Power estimations for all secondary outcomes are based on the decided inclusion of 185 patients, expected standard deviation and established minimal clinical important difference (MCID) (**Table 2**).

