**3.6.1 Statistical analyses plan**

Analyses of the outcomes will be performed by the trial statistician ([name]) who is blinded to the treatment allocations. Secondary analyses will be performed by Postdoctoral fellow, PhD [name].

Baseline data will be reported as averages and standard deviations (medians and interquartile ranges) or frequencies and proportions as appropriate. Data analyses of both primary and secondary endpoints will be performed using intention-to-treat analyses. Additionally, per-protocol analyses including patients who complete  $\geq 70\%$  of the PTR and HPR rehabilitation program will be performed. Reporting will follow the CONSORT (Consolidated Standards of Reporting Trials) Statement for non-pharmacologic trials. Differences between the groups' changes of primary and secondary outcomes (10-weeks from baseline; 35-weeks from baseline and 75-weeks from baseline) will be analyzed by mixed effect models. The models include adjustment for treatment groups, age, sex, BMI, FEV1, Charlson Comorbidity Index and smoking status, and a random effect recruitment site. To account for possible regression to the mean effect, the baseline measure for the outcome will be included as a fixed effect variable in the models. Normal distribution of the model residuals is evaluated by inspection of Q-Q plots. All data are considered missing at random and because of this, the ignorability assumption for the likelihood estimator is used to account for missing data. The number of used datasets will be transparent. Survival are visualized by Kaplan-Meier curves. Group differences on number of patients being adherent, hospitalization and death are analyzed using chi-squared test. No interim analysis will be made. Statistical analyses are carried out using R 3.2.2 (R Foundation for Statistical Computing, Vienna, Austria). P-values of less than 0.05 are considered statistically significant.

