### **3.6.2 Randomization**

The randomization allocation to HPR, PTR, CON is performed using block randomization with a randomized block size of 6 and 12 in random order. The randomization list will be generated in REDCap by the trial statistician and is not accessible to investigators involved in the conduct of the study until the database has been unlocked.

After written informed consent and completion of study assessments, patients are randomized to either HPR, PTR or CON. The target number of patients randomized to each group is 70, 70 and 45 respectively. After identification of an eligible patient, the patient is assigned a randomization number as identifier throughout the study. The participants are informed about which group they are randomized to by email and phone call. The patients in the three groups begin their assigned intervention within seven to ten days after randomization.

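### Protocol section 3.6: the stated inputs do not yield 36 controls; a two-sided test of 56 vs 36 has 73% power, and 80% needs 49 controls

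*Protocol*

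**What the plan says.** Protocol section 3.6 names three primary pairwise comparisons on the COPD Assessment Test: equivalence of the two programmes, and superiority of each programme over control. The equivalence calculation comes first and gives 56 per intervention arm. For superiority, the section says that "a minimal clinical difference of 2.5, SD of 4.5, power of 80% and significance level of 5% were used in a two-sample t-test", with the intervention arms held at 56, and concludes: "This yields a necessary size of 36 patients in the control group".

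Each group is then enlarged by 25%, to cover both withdrawal and power lost through adjustment, giving 70/70/45 and 185 in total. Section 3.6.2 repeats this as the recruitment goal: "The target number of patients randomized to each group is 70, 70 and 45 respectively".

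No sentence says whether the superiority tests are one- or two-sided. Section 3.6.1 says only: "P-values of less than 0.05 are considered statistically significant".

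**The concern.** Every input to the control-arm calculation is printed, so a reader can repeat it, and the result is not 36. The number matters because it fixes the size of the control arm, which serves two of the three primary comparisons, and because 45 is simply 36 enlarged by a quarter.

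On the two-sided reading, the chance of missing a true 2.5-point benefit in either superiority test is 27% at the sizes the protocol calls necessary, not the 20% implied by its power statement. Anyone interpreting a non-significant superiority result would be relying on a power that the stated calculation does not deliver.

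**Working it through.** **Inputs (all from protocol section 3.6).** Difference δ = 2.5; SD σ = 4.5; level 5%; power 80%; two-sample t-test; intervention arm n₁ = 56. Standardised difference: 2.5 / 4.5 = 0.556.

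**1. The protocol's equivalence figure.** Two one-sided t-tests at 5% each, margins ±2.5, true difference 0, SD 4.5, 56 per arm: power 79.8% (57 per arm gives 80.7%). The 56 therefore reproduces to within one patient, and the fault lies in the control-arm step alone.

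**2. Power at 56 vs 36.** The non-centrality parameter is

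λ = (δ/σ) / √(1/n₁ + 1/n₂) = 0.556 / √(1/56 + 1/36) = 2.60, with 56 + 36 − 2 = 90 degrees of freedom.

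- Two-sided 5%: critical value 1.987, power 73.0% (normal approximation 73.9%).
- One-sided 5%: critical value 1.662, power 82.5%.

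**3. Controls needed for 80% with 56 fixed.** The normal approximation solves 1/n₂ = [(δ/σ) / (z for the level + z for the power)]² − 1/56.

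- Two-sided: (0.5556 / (1.960 + 0.842))² = 0.03932; 0.03932 − 0.01786 = 0.02147; n₂ = 46.6, so 47.
- Exact two-sided t-test: 48 gives 79.9% and 49 gives 80.3%, so 49.
- Exact one-sided t-test: 31 gives 79.3% and 32 gives 80.0%, so 32.

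| Reading of the 5% level | Controls needed | Power at 56 vs 36 |
|---|---|---|
| Two-sided | 49 | 73.0% |
| One-sided | 32 | 82.5% |
| Protocol | 36 | 80% |

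Neither reading returns 36. Pooling both programmes (112 patients) against control would need 34 on a two-sided test, which is close to 36, but section 3.6 describes a separate test for each programme with 56 patients.

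**4. What 45 randomised controls deliver (two-sided, unadjusted).** 36 × 1.25 = 45 and 56 × 1.25 = 70.

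| Evaluable share of 70 vs 45 | Power |
|---|---|
| 100% | 82.2% |
| 95% | 80.2% |
| 90% | 78.0% |
| 80% (56 vs 36; whole allowance used) | 73.0% |

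The protocol's factor applied to the corrected number gives 49 × 1.25 = 61.25, so 62 controls and 70 + 70 + 62 = 202 patients, against 45 and 185.

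**The case against.** **Sidedness.** The shortfall depends on a two-sided test, which the protocol never specifies. With a one-sided 5% test, 56 vs 36 has 82.5% power and is not short at all. The neighbouring equivalence calculation also uses 5% per side. This objection stands to the extent that the 73% must be presented as conditional. It does not rescue the 36, because the one-sided requirement is 32. Two-sided is also the ordinary reading of a 5% t-test judged at P < 0.05. Table 2 mostly agrees: at about 65 vs 42 patients, two-sided tests reproduce its powers for HADS, BPI, walking distance, sit-to-stand, timed up and go, gait speed and grip strength. Only EQ5D-VAS and steps per day fit a one-sided test.

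**The 25% allowance.** It covers loss of power from adjustment as well as withdrawal, and the split is not given. A 20% loss of patients is therefore not the protocol's planned attrition, and 73% marks the case where the whole allowance is used. With about 5% loss or less, 70 vs 45 still reaches 80%. This stands.

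**The planned analysis.** Section 3.6.1 specifies a mixed model with the baseline value as a covariate, which may be more efficient than a t-test. As an assumption, suppose 4.5 is the unadjusted SD of the week-10 score, so that adjustment multiplies it by √(1 − ρ²). Power at 56 vs 36 is then 77% for a baseline correlation ρ of 0.3, 80% for 0.4 and 84% for 0.5. If 4.5 is already the SD of a change or an adjusted SD, there is less to gain. The protocol does not say which SD it is, gives no correlation, and counts adjustment as a loss of power. A reader might infer that the trial itself is underpowered for superiority; the documents support only that the stated calculation is wrong.

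**Joint power.** A reader might also infer from the hypotheses in section 2.1.2 that all three primary tests must succeed together, and object that the chance of this is low. If both programmes truly gain 2.5 points, simulation gives about 52% at 56/56/36 and about 68% at 70/70/45. But section 3.6 sizes each comparison on its own, the protocol sets no rule that all three must succeed, and it claims no joint power. There is no stated figure here to correct.

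**Conclusion.** The point holds as an error in the stated sample-size calculation for two of the three primary comparisons. A difference of 2.5, SD 4.5, a 5% level, 80% power and 56 fixed per intervention arm do not yield 36 controls under a one- or two-sided two-sample t-test, and no other section corrects the figure. On the two-sided reading the stated power is seven points too high at 56 vs 36 (73.0% against 80%), and the necessary control number is 13 too low (36 against 49).

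This rests on the printed inputs, equal SDs in the arms, an unadjusted comparison and a two-sided test; the last is the ordinary reading but is not written down. The power actually achieved will depend on retention and on what baseline adjustment gains, and neither can be fixed from the document. The type I error, endpoint, equivalence margin and planned analysis are unaffected.

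**What to change.** In section 3.6, state that each superiority test is two-sided at 5%. Then do one of the following:

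- Keep 70/70/45 and replace the 80% claim for superiority with the power delivered by the unadjusted t-test: 73% at 56 vs 36 evaluable, and 82% only with full follow-up of 70 vs 45.
- Correct the necessary control number from 36 to 49. With the protocol's own 25% increase this means about 62 randomised controls and about 202 patients in total, and section 3.6.2 must change to match.

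The first option is a change of wording and needs no extra patients; its cost is a less favourable power statement. The second costs about 17 more controls (62 − 45). If the sponsor wants to rely on baseline adjustment to recover power, section 3.6 should say which SD the 4.5 is and what baseline correlation is assumed.

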**3.6.1 Statistical analyses plan**

Analyses of the outcomes will be performed by the trial statistician ([name]) who is blinded to the treatment allocations. Secondary analyses will be performed by Postdoctoral fellow, PhD [name].

Baseline data will be reported as averages and standard deviations (medians and interquartile ranges) or frequencies and proportions as appropriate. Data analyses of both primary and secondary endpoints will be performed using intention-to-treat analyses. Additionally, per-protocol analyses including patients who complete  $\geq 70\%$  of the PTR and HPR rehabilitation program will be performed. Reporting will follow the CONSORT (Consolidated Standards of Reporting Trials) Statement for non-pharmacologic trials. Differences between the groups' changes of primary and secondary outcomes (10-weeks from baseline; 35-weeks from baseline and 75-weeks from baseline) will be analyzed by mixed effect models. The models include adjustment for treatment groups, age, sex, BMI, FEV1, Charlson Comorbidity Index and smoking status, and a random effect recruitment site. To account for possible regression to the mean effect, the baseline measure for the outcome will be included as a fixed effect variable in the models. Normal distribution of the model residuals is evaluated by inspection of Q-Q plots. All data are considered missing at random and because of this, the ignorability assumption for the likelihood estimator is used to account for missing data. The number of used datasets will be transparent. Survival are visualized by Kaplan-Meier curves. Group differences on number of patients being adherent, hospitalization and death are analyzed using chi-squared test. No interim analysis will be made. Statistical analyses are carried out using R 3.2.2 (R Foundation for Statistical Computing, Vienna, Austria). P-values of less than 0.05 are considered statistically significant.

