#### **3.2 Study population**

A total of 185 patients with moderate to very severe COPD who are unable to access the conventional hospital- and community-based PR programs when offered during routine consultations will be included from seven hospitals in the Capital Region, through general practitioners, healthcare centers and advertising through the Danish Lung Association to get a broad representative sample fulfilling our defined inclusion and exclusion criteria. During inclusion, baseline self-reported symptoms, functional capacity and physical activity is measured. Hereafter each participant is randomly assigned to one of the three arms in the study; HPR, PTR or CON. The HPR and PTR interventions begin within seven-to-ten days after randomization and patients participate in the 10-week assigned intervention and thereafter continue in a self-maintenance program for another 65-weeks (approx. 15-months). Self-reported respiratory symptoms constitute the primary outcome, assessed at the 10-week follow-up visit (primary endpoint). Follow-up assessment are done 10, 35 and 75 weeks (primary endpoint for the maintenance study) from baseline.

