## **3.7 Interventions (also read figures in appendices 1)**

### **3.7.1 Pulmonary Tele-Rehabilitation (PTR)**

The PTR intervention is supervised by skilled physiotherapists and respiratory nurses with at least 2-years of substantial experience with PR and delivered via a virtual platform at Bispebjerg and Hvidovre Hospital to a group of 4–6 patients who exercise at home and communicate via tablet with Center for IT and Medico (CIMT) approved communication software. Each session is 60 min; 35 min of exercise and 25 min of patient education, two times per week for the duration of 10 weeks. The specific exercises used are evidence-based as they have been used in several intervention studies on patients with severe or very severe COPD and involves larger muscle groups with 50/50% exercises for upper and lower extremities, respectively. Volume, intensity and content specified for the exercise protocol is in accordance with both national and international exercise recommendations. The exercise sessions include relative progression every fourth week, as the patients are expected to improve their mental and physical capacity during the intervention. Additionally, to the supervised program, patients are instructed to do daily physical activity of at least 30 minutes by modalities accessible to the patient, e.g. in- or outdoor walking activities in bouts of minimum 10 minutes.

Every second session of the patient education consists of 25 minutes of Mindfulness-based Cognitive Therapy (MCBT) exercises and education developed for COPD patients with the potential mediating effects of mindfulness, self-compassion and breathlessness catastrophizing. The other education sessions consist of dialogue reflections around empowerment of the subjects: action-plan for symptom deterioration, medication-technic and correct use, better living with COPD, nutrition and importance of smoking cessation.

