### **3.7.2 Home-based Pulmonary Rehabilitation (HPR)**

The HPR intervention is an individual self-initiated home-based PR program with motivational and professional counseling, supported by health technology e.g. telephone call and facetime with choice of preference. The first session is a home visit by an experienced respiratory physiotherapist/nurse. During the visit the physiotherapist/nurse works with the patient to establish exercise goals, write a formal exercise prescription of four to six exercises, provide a mindfulness program and education in use of a home diary and assess inhaler technique. The physiotherapist also supervises the first exercise and mindfulness session. The patient is informed that performing the self-initiated exercise and mindfulness program is likely to improve their symptoms, fitness and physical functioning.

The overall goal is for the patient to achieve at least 30 minutes of self-initiated muscle-endurance based exercise three days a week. The prescribed physical exercises are available on the tablet as an instructed exercise-film. Secondly the patient is instructed to complete a mindfulness program of choice for 15 minutes at least once a week. Seven mindfulness exercises are available from sound-files on the tablet for self-initiated mindfulness-sessions.

Additionally, daily physical activity of at least 30 minutes by modalities accessible to the patient, e.g. in- or outdoor walking activities in bouts of minimum 10 minutes. During the initial visit the physiotherapist/nurse accompanies the participant on their initial walk (weather permitting for those who had chosen to walk outside the home). This allows planning of an appropriate route around the local neighborhood consistent with the patient's abilities (e.g. ability to walk stairs/hills).

In a home diary the patient is instructed to record when, where and how often she/he plans to perform exercise and mindfulness; what might get in the way of the plans this week; and what can be done to overcome any perceived barriers. The diary includes a telephone number so the patient can contact the physiotherapist/nurse between sessions if required to answer questions related to the program. During the initial home visit the physiotherapist/nurse also assesses safety of the home environment in relation to the exercise program.

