| Pulmonary Tele-Rehabilitation (PTR)       | 
 
• The PTR intervention is supervised by skilled physiotherapists and respiratory nurses.
 
• Delivered via a webcam CIMT approved communication software from Bispebjerg Hospital
 
• In groups of 4–6 patients; exercise at home and communicate via tablet for 10 weeks
 
• Each session is 60 min; 35 min of exercise and 25 min of patient education/ mindfulness
 
• Patients are instructed to do daily physical activity of at least thirty minutes of physical activity e.g. in- or outdoor walking activities of in bouts of minimum 10 minutes.
 
• Every second session consists of 25minutes of Mindfulness-based Cognitive Therapy (MCBT) exercises and education developed for COPD patients with the potential mediating effects of mindfulness, self-compassion, breathlessness, catastrophizing. The education session consists of dialogue reflections around empowerment of the patients: action-plan with symptom increase, medication-technic and correct use, better living with COPD, nutrition, importance of smoking cessation.
 
• The physical exercises are available on the tablet as an instructed exercise-(film)video for self-initiated exercising. The mindfulness exercises are available from sound-files on the tablet for self-initiated mindfulness-guidance.
 
• Education materials are delivered in paperback together with tablet and exercise equipment but also available as audio-book chapter on tablet in layman language.
 
• Exercise equipment is a package containing a step-box and pairs of dumbbells weight from 1 to 5 kilo (heavier dumbbells available on request).
 
 |

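### Site is the only random effect named: weeks 35 and 75 have no stated link to earlier post-baseline visits, and PTR group delivery is in neither the model nor the sample size

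*Protocol*

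**What the plan says.** Section 3.6.1 of the protocol applies mixed effect models to changes at "10-weeks from baseline; 35-weeks from baseline and 75-weeks from baseline". The fixed part is treatment group, age, sex, BMI, FEV1, Charlson index and smoking status. The outcome's baseline value enters as a covariate: "the baseline measure for the outcome will be included as a fixed effect variable in the models". The random part is "smoking status, and a random effect recruitment site". No patient effect, within-patient covariance, visit term, treatment-by-visit term or exercise-group effect is listed. For missing values, MAR is assumed and "the ignorability assumption for the likelihood estimator is used to account for missing data".

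Section 3.2 makes CAT the primary outcome, "assessed at the 10-week follow-up visit (primary endpoint", and names week 75 as the primary endpoint of the maintenance study.

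On delivery, section 3.7.1 provides PTR live "to a group of 4–6 patients who exercise at home", and the PTR row of Appendices 1 agrees: "In groups of 4–6 patients; exercise at home and communicate via tablet for 10 weeks". Section 3.7.2 differs: "The HPR intervention is an individual self-initiated home-based PR program". After week 10, section 3.7.4 offers weekly supervised maintenance sessions, also in groups of 4 to 6, and the control row of Appendices 1 offers that programme to controls.

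The sample size in section 3.6 rests on t-tests with independent patients. Its 25% increase is for withdrawal and adjustment; clustering is not mentioned.

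**The concern.** Two separate matters arise from the same short list of random effects.

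**Visits.** Likelihood under MAR uses a patient's earlier results only if the model links that patient's visits. Baseline is a covariate here, not a repeated outcome, and no patient-level term is named. Under separate visit models, a patient missing at week 75 contributes nothing to that analysis, whatever was seen at weeks 10 and 35. Under one shared model without within-patient covariance, three correlated values count as independent. The first puts the maintenance endpoint at risk of bias. The second would make an effect averaged over visits look too precise.

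**PTR groups.** Up to week 10, patients in one arm share sessions, therapists and peers, and their outcomes may be correlated. That arm enters two of the three primary comparisons, including equivalence with HPR. Ignoring positive correlation makes the interval too narrow, and in an equivalence test a narrow interval favours the claim.

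**Working it through.** **1. The plan's own figure.** Inputs from section 3.6: margin 2.5, SD 4.5, power 80%, level 5% (each one-sided test at 5%), true difference 0.

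n = 2 × (4.5/2.5)² × (1.645 + 1.282)² = 55.5, so 56 per arm, as stated. Full two-one-sided-test power at 56 per arm is 0.805. The base calculation is sound for independent patients.

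**2. Separate model per visit: missing data.** The protocol gives neither a dropout mechanism nor a between-visit correlation, so both are assumed. Simulation: 4,000 trials per scenario, 70 active against 45 control, true effect -2.5, residual SD 4.5, correlation between weeks 10 and 75 of 0.5 or 0.7, and roughly 25% to 29% lost at week 75. The joint analysis also uses the week-10 value.

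| Dropout depends on week-10 result | Week 75, visits not linked | Week 75, joint likelihood |
|---|---|---|
| not at all | -2.50 | -2.50 to -2.51 |
| equally in both arms | -2.48 to -2.51 | -2.48 to -2.51 |
| active arm only | -3.01 to -3.26 | -2.48 to -2.51 |
| in opposite directions by arm | -3.33 to -3.63 | -2.49 to -2.51 |

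A second simulation (correlation 0.7, about 20% to 25% lost, dependence in the active arms only) gave -2.86 unlinked and -2.51 joint.

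For week 10, missingness was made to depend on baseline and arm. The baseline-adjusted model without a patient effect averaged -2.46 to -2.52. The primary endpoint is therefore not affected under that mechanism.

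**3. One shared model: standard errors.** The mean of three visits with correlation ρ has variance SD²(1 + 2ρ)/3. Independence gives SD²/3. The standard error is too small by √(1 + 2ρ). For assumed ρ of 0.3 to 0.7 this is 1.26 to 1.55, and two-sided error would be 12% to 21% instead of 5%. This applies only to an effect averaged over visits. A contrast at a single visit uses one record per patient and is not inflated this way.

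**4. PTR groups up to week 10.** The ICC is not given; 0.01 to 0.10 is assumed. With m patients per group, DE = 1 + (m - 1) × ICC in the PTR arm only. The variance of PTR minus HPR is 4.5² × (DE + 1)/56. If clustering is ignored, one-sided error is 1 - Φ(1.645/√((DE + 1)/2)).

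| m | ICC | DE | Effective PTR n | One-sided equivalence error | Power at 56/56 |
|---|---|---|---|---|---|
| 4 | 0.01 | 1.03 | 54.4 | 5.1% | 0.797 |
| 5 | 0.02 | 1.08 | 51.9 | 5.3% | 0.784 |
| 5 | 0.05 | 1.20 | 46.7 | 5.8% | 0.753 |
| 5 | 0.10 | 1.40 | 40.0 | 6.7% | 0.701 |
| 6 | 0.10 | 1.50 | 37.3 | 7.1% | 0.675 |

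Example, last row: √((1.50 + 1)/2) = 1.118; 1.645/1.118 = 1.471; upper tail 0.071. Over the same range, two-sided error for PTR against control (56/36) is 5.1% to 7.3%.

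**The case against.** The strongest reply has five parts.

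- **Independence across visits is not stated.** Section 3.6.1 speaks of models in the plural, takes each change from baseline, and lists no visit term. One model per visit is a natural reading. Each patient then has one record, and a patient effect could not be estimated. This stands. A reader might infer that the plan treats repeated visits as independent; the protocol does not settle that, and it names no visit-averaged effect.
- **The likelihood approach is sound at week 10.** No earlier post-baseline value exists to borrow. A reader might infer that the missing-data statement fails altogether; for the primary endpoint it does not. This stands.
- **Week-75 bias is conditional.** It needs dropout that depends on week-10 response differently by arm. With equal dependence the unlinked analysis was unbiased in the simulations. This stands. Such a difference is nevertheless plausible, because after week 10 the intervention arms continue a programme, while controls choose between joining it and remaining controls.
- **Stable PTR groups are assumed.** Seventy PTR patients over 18 to 24 months (about 78 to 104 weeks) is 70/104 = 0.7 to 70/78 = 0.9 per week, and section 3.6.2 has patients start within 7 to 10 days. Membership may roll, and then the simple design effect is only approximate. This stands as a caution about size. Shared sessions would still induce correlation.
- **Covariance structure often belongs in a statistical analysis plan, and none is shown.** This stands in part. The protocol does more than stay silent, however: it lists a specific model with site as its only random effect and rests the missing-data claim on it.

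**Conclusion.** The point holds in limited form. As written, the model gives weeks 35 and 75 no stated way to use earlier post-baseline results. The week-75 maintenance endpoint is then biased if dropout depends on week-10 response differently by arm: about -2.9 to -3.6 for a true -2.5 in the assumed scenarios, and no bias when the dependence is equal. If the visits share one model instead, standard errors are too small for an effect averaged over visits only. The week-10 primary analysis is valid under MAR given arm, baseline and covariates.

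PTR clustering up to week 10 is in neither the model nor the sample size, whichever way the visits are modelled. Its effect is small at low ICC (5.1% error and about 80% power at 0.01) and material at 0.10 (up to 7.1% and down to about 68%). These figures rest on an assumed ICC and fixed groups. They do not show that the model is invalid. The plan should be changed because a better method is available at little cost.

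**What to change.** 1. State one longitudinal model for weeks 10, 35 and 75, with treatment-by-visit and baseline-by-visit terms, the listed covariates, unstructured within-patient covariance and site. Take the week-10 and week-75 contrasts from it. The ignorability statement then makes use of earlier visits.
2. For week-10 contrasts involving PTR, add a partially nested random effect for PTR exercise group, at least as a sensitivity analysis over a range of ICCs. With 70 patients there would be only about 12 to 18 groups (70/6 to 70/4), so an estimated ICC will be imprecise and fixed values are useful.
3. Record PTR group and maintenance group membership, including changes, in the eCRF from the start.
4. Do not treat HPR and control patients as single-member clusters at weeks 35 and 75. Maintenance sessions are also held in groups and are offered to controls.

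The cost is a change of analysis wording, one or two eCRF fields, and slightly wider intervals for PTR contrasts if the ICC is low. At the top of the assumed range the widening is about 12% (standard error ratio 1.118).
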